### Inclusion and Exclusion Criteria

Participants will be eligible for the study if they are enrolled in a course at York University that provides course participation credit via study enrolment through the Undergraduate Research Participant Pool website. On the recruitment website as well as on the consent form, we have explained that the study may require use of a smartphone-based task. Participants with self-reported cardiac conditions (eg, cardiac arrhythmias, coronary artery disease, and pacemaker) will be excluded as they contravene the interpretation of vagal-mediated HRV [31]. Participants in this study will have no prior relationship with the researchers, including participation in classes by faculty members on the research team.

### Procedures

#### Group Classification and Randomization

Upon signing up for the study, participants will be instructed to arrive to the Human Pain Mechanisms Lab at York University, where the study procedures will be explained, and informed consent will be obtained from all participants. Participants will complete prescreening questionnaires for CP, depression, or anxiety symptoms. A research assistant will score the questionnaire once completed and check to see if the participant meets *severe* criteria for depression symptoms (≥21 on the Centre for Epidemiological Studies Depression Scale) [32] or anxiety symptoms (≥36 on the Beck Anxiety Inventory) [33]. If they meet such criteria, they will be classified into the depression-anxiety group and randomized to the MMA (MMA+) or no app (MMA−) condition. If the participant reports having a CP condition (>3 months of pain on the Brief Pain Inventory) [34], they will be classified into the CP group and randomized to MMA+ or MMA−. Participants who do not meet the criteria for CP or severe depression-anxiety symptoms will be classified into the CF group and randomized to MMA+ or MMA−.

A 3-block randomization schedule (CP, depression-anxiety, and condition free) with 2 treatment arm allocations (MMA+ and MMA−) was created by the study coinvestigator (study author [name]) using a randomization sequence generator [35]. The randomization schedule uses a 1:1 ratio with blocks of 10. Treatment allocation will be determined by study coordinators and staff members after participants complete their prescreening questionnaires to determine their group classification (Figure 2). Study research assistants review prescreening questionnaires and assign the grouped participants to their corresponding treatment arm using a randomization schedule column concealed in a computer spreadsheet using the *highlight* (black) function. Upon entering participants into the spreadsheet, research assistants unhighlight the next available cell in the corresponding column to reveal their treatment assignment.

#### Experimental Session

Participants will undergo a 3-phase (baseline, stress induction, and MM) assessment during which electrocardiogram (ECG) and respiration rate data will be collected for later HRV analysis (Figure 3). A mobile cardiogram system by MindWare (MindWare Technologies, LTD) will be used, requiring placement of 3 adhesive electrodes on the right clavicle and left and right hipbones and a respiratory belt secured around the participant’s waist.

**Figure 3 figure3:**
[figure not shown]
Study procedures. Physiological assessments are in red boxes, and questionnaire assessments are in gray boxes. BAI: Beck Anxiety Inventory; BPI: Brief Pain Inventory; CES-D: Center for Epidemiology Depression Scale; FFMS: Five-Factor Mindfulness Scale; HRV: heart rate variability; MWI: Mind-Wandering Inventory; PARS: Present Moment Awareness Rating Scale; POMS: Profile of Mood States; SDRS-5: Social Desirability Rating Scale-5; SUDS: Subjective Units of Distress Scale. TMS: Toronto Mindfulness Scale.

##### Rest Phase

The first phase will comprise a 5-min baseline period during which participants will rest quietly with their eyes closed and not speak or make sudden movements.

##### Stress Induction Phase

Following the baseline phase, a 5-min stress induction procedure will be performed whereby the participant engages in a set of mental arithmetic tasks, with the instruction to work as quickly as possible for maximal performance. Mental arithmetic was chosen as a stressor task because of its superior properties in eliciting sympathetic responses compared with other laboratory-based stressors [36].

##### Post-Stress Meditation Phase

After the stress induction phase, a post-stress MM phase will involve either the MMA+ or MMA− task according to the randomization schedule.

After completing the prestudy set of questionnaires, participants will be randomized to either the smartphone-based MMA+ or a mindful breathing practice without use of a mobile app (MMA−). Mindful breathing instructions will involve paying attention to breathing sensations while seated with eyes closed for 12 min and reorienting attention back to breathing once aware of mind wandering [2]. Research assistants remain in the room during the intervention phase, for both intervention conditions, to ensure there are no technical or practical issues with the interventions. There are no adverse events expected during the study, and participants are free to withdraw their participation at any time during the study with no penalty to their research credit or any other costs.

### Intervention Arm: Mindfulness Meditation With the App

The MMA was developed using JavaScript and installed on an iPhone 4s. As the app was designed with young adults in mind, the leading thought was to keep the intervention brief and the design simple and easy to use. Participants are asked to hover their thumbs on 2 buttons, *breath* and *other*, presented on a white screen for the duration of the task (Figure 1). The MMA is a 12-min breath awareness task that involves a total of 24 silent phases comprising 6 different durations (5 seconds, 15 seconds, 25 seconds, 35 seconds, 45 seconds, and 55 seconds) randomly presented 4 times each and followed by the presentation of a 1-second tone. During the silent phases, participants are to practice mindful breathing with their eyes closed by paying attention to their breathing sensations and reorienting their attention when noticing their mind wandering. At the sound of the tone, participants press *breath* if, in that moment, they were attending to their breath, or *other* if they were attending to other experiences. Participants are instructed to return their attention to mindful breathing after pressing 1 of the 2 buttons on the screen. The app was designed to record reaction time from tone onset to button press and the number of times *breath* and *other* buttons were pressed. A prototype was first tested internally, and feedback was gathered from the research team and pilot participants to ensure a smooth user experience without technical bugs. Feedback influenced decisions regarding the number of tones and interval between tones played, the size of the *breath* and *other* buttons, and the addition of a 1-min trial period before commencing the 12-min meditation task.

Participants in the MMA+ condition will use the MMA to practice mindful breathing with the following instructions: “For the duration of the task, pay attention to your breathing sensations, including (1) the feeling of the air passing through your nostrils, (2) the movement of your in-and-out breath at your chest and torso, (3) the sound of the air as you breathe in and out, (4) the temperature (coolness or warmth) of the in-and-out breath, and (5) returning your attention to your breath when you have noticed your attention has been elsewhere.” In addition, amidst mindful breathing practice, they will be asked to press a *breath* (I am paying attention to my breath) or *other* (I am not paying attention to my breath) button on the phone screen when hearing a tone introduced at random intervals. The MMA task will involve a total of 24 silent phases of 6 different durations (5 seconds, 15 seconds, 25 seconds, 35 seconds, 45 seconds, and 55 seconds) randomly presented 4 times each and followed by the presentation of the tone. Participants are provided a 1-min practice session with the app before the intervention session. Participants will engage in smartphone-based mindful breathing for 12 min in a seated and eyes closed position.

### Control Arm: Mindfulness Meditation With No App

Participants in the MMA− condition will engage in mindful breathing without use of the smartphone app for 12 min in a seated and eyes closed position.

### Measures

#### Heart Rate Variability

There are several metrics that quantify HRV, the majority of which are either time based or frequency based. With the beat-to-beat interval series (also referred to as the R-R series), one can estimate the square root of the mean of squared successive differences between interbeat intervals (IBI), which has been found to be strongly correlated with respiration-based heart rate (HR) changes) [37]. It is important to note that both the IBI and the standard deviation of IBI’s are subject to increases with longer ECG recordings (influenced by slower, long-range fluctuations in HR independent of respiration-induced beat-to-beat changes). Thus, the Task Force [38] has recommended 5 min as a standardized length of HRV assessment in clinical and psychophysiological research. Using the frequency domain measure, one can examine the extent to which the HR varies within specific frequency ranges. The Fourier transform method deconstructs the time domain representation of the R-R series and computes a measure of *power* in several frequency bands in units of milliseconds squared (ms^2^). These bands include ultralow frequency (<0.04 Hz), low frequency (0.04-0.15 Hz), and high frequency (HF; 0.15-0.4 Hz). Typically, the frequency band of interest for the purposes of HRV interpretation is the HF band, as this is where the respiratory-linked beat-to-beat changes are reflected [37,39]. Although this is not intended to be an exhaustive account of HRV metrics, the aforementioned measures are the most commonly used in studies of vagal influence on cardiac chronotropy. On the basis of the recommendations by the 2 international committees [38,40], this study focuses on the frequency measure as the primary measure to interpret changes in vagal-mediated HRV across different conditions.

ECG recordings will be collected using MindWare Impedance Cardiograph acquisition system and used to analyze HF-HRV as the primary HRV measure. The MindWare system utilizes 3 adhesive electrodes applied to the right collarbone (negative lead) and the lower left and right ribs (positive lead and ground lead) or alternatively the wrists (positive and negative leads) and ankle (ground lead) if necessary. MindWare BioLab and HRV software will be used to calculate time- and frequency-based HRV metrics. Patients will be measured during phases of (1) rest in a seated position with eyes closed (5 min), (2) a stress induction task requiring rapid completion of arithmetic problems (5 min), and (3) meditation conditions of MMA+ or MMA−.

#### Respiration Rate

A MindWare respiratory belt (below the sternum) will be used to monitor respiration rate during rest, stress induction, and meditation. Respiration is a potential confounding variable for HRV interpretation and will be used as a covariate in HRV analyses if it is found to differ between assessment phases or study groups [31].

#### Breath Focus and Reaction Time

Using data collected with the MMA+, breath focus will be measured using the ratio of *breath* and *other* responses during the MMA+ task. Reaction time measures will also be collected pertaining to mean (seconds) in pressing *breath* and *other* buttons during the MMA+ task.

#### Prescreening Questionnaires

The following prescreening questionnaires will be administered to students to determine group classification by assessing for clinical CP (The Brief Pain Inventory), depression (The Center for Epidemiological Studies-Depression Scale), and anxiety symptoms (Beck Anxiety Inventory).

##### Brief Pain Inventory—Short Form

The Brief Pain Inventory is a 16-item, self-report questionnaire that measures pain intensity and pain interference. The test has good internal consistency (alpha=.85) and high test-retest reliability [41].

##### Center for Epidemiological Studies Depression Scale

The Center for Epidemiological Studies Depression Scale (CES-D) is a screening test for depressive symptoms with good sensitivity and specificity and high internal consistency [32]. The CES-D has been found acceptable and reliable in adolescent and young adult populations [42].

##### Beck Anxiety Inventory

The Beck Anxiety Inventory is a 21-question multiple-choice self-report questionnaire that is used for measuring anxiety severity. Internal consistency (Cronbach alpha) ranges from .92 to .94 for adults and test-retest (1-week interval) reliability is 0.75 [33].

#### Secondary Outcomes and Trait Questionnaires

Participants will also be asked to complete the following questionnaires to assess mood (Profile of Mood States [POMS]), present moment awareness (Present Moment Awareness Ratings Scale [PMARS]), mind-wandering (Mind-Wandering Inventory [MWI]), state mindfulness (Toronto Mindfulness Scale [TMS]), trait mindfulness (Five Factor Mindfulness Scale), social desirability (Social Desirability Response Set 5-Item Survey), and subjective stress (Subjective Units of Distress Scale [SUDS]).

##### Profile of Mood States

The POMS is a 37-item questionnaire designed to assess global distress as well as 6 mood states: fatigue, vigor-activity, tension-anxiety, depression, anger-hostility, and confusion-bewilderment. Participants are asked to indicate the degree to which they have experienced different mood states in the past week. The scale has good internal consistency (alpha=.91) and test-retest reliability (*r*=0.74). The POMS has been validated for use in adolescents and adults [43]. Higher total scores represent greater total mood disturbance [44].

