**Objective:**

This study aims to evaluate the psychophysiological effects of the MMA. Specifically, the study will assess parasympathetic functioning using heart rate variability (HRV; primary outcome), pain and mood symptoms, mind-wandering and present moment awareness, and breath focus in groups of undergraduate participants who self-report clinically-relevant symptoms of chronic pain (CP) and depression or anxiety (DA) and condition-free (CF) participants who do not meet either criteria. We hypothesize that use of the MMA by study groups will lead to improved HRV, pain, and mood symptoms compared with groups who do not use the app.

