#### Hypothesis 2b

CP, DA, and CF participants receiving MMA+ will report significantly lower mind wandering than corresponding participants receiving MMA−, reflecting the potential for MMA+ to make participants more able to recover their attention from mind-wandering contents and processes during MM.

#### Hypothesis 3

CP and DA participants randomized to the MMA+ condition will demonstrate significant reductions in mood symptoms (state depression and anxiety) after the MM task compared with CP and DA participants randomized to the MMA− condition, reflecting the potential for MMA+ to facilitate the emotion regulation effects of MM for clinical populations.

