##### Subjective Units of Distress Scale

The SUDS is a means of rating the severity of current distress (or anxiety), allowing for the monitoring of changes over time, where 0 is feeling perfectly relaxed and 100 is the worst anxiety and stress imaginable [50]. Participants will be asked to provide 0 to 100 SUDS ratings at baseline, post-stress induction, and after the post-stress meditation phases. The SUDS ratings will be used to do a manipulation check with respect to the mental arithmetic stressor and to monitor changes in stress over time.

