#### Hypotheses 2a and 2b

To analyze pre-post increases in levels of present moment awareness, state mindfulness, and mind wandering, separate 3-way repeated-measures ANOVA with group (CP, DA, and C), time (pre and post), and condition (MMA− and MMA+) will be used with simple main effects to examine significant interactions.

#### Hypothesis 3

To analyze pre-post changes in mood, a 3-way ANOVA with group (CP, DA, and C), time (pre and post), and condition (MMA− and MMA+) will be used with simple main effects to examine significant interactions.

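### Hypothesis 3 tests state mood across one 12-minute session with a mood scale described as rating the past week, and the abstract promises a pain effect for which the body gives no outcome or analysis

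*Protocol article*

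**What the plan says.** **Mood.** Under Secondary End Points, Hypothesis 3 states that chronic pain (CP) and depression-anxiety (DA) participants given the app "will demonstrate significant reductions in mood symptoms (state depression and anxiety) after the MM task", compared with those not given it. The planned test, under Statistical Analyses of Outcomes, reads "To analyze pre-post changes in mood, a 3-way ANOVA with group", with time (pre and post) and condition as the other two factors. The list in Secondary Outcomes and Trait Questionnaires assigns one instrument to mood, the POMS. Its own section says: "Participants are asked to indicate the degree to which they have experienced different mood states in the past week".

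The article also collects a rating of current distress or anxiety, the SUDS: "Participants will be asked to provide 0 to 100 SUDS ratings at baseline, post-stress induction, and after the post-stress meditation phases". Its stated uses are a manipulation check on the stressor and the tracking of stress over the session. It is not assigned to Hypothesis 3.

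**Pain.** The abstract's Objective says "the study will assess parasympathetic functioning using heart rate variability (HRV; primary outcome), pain and mood symptoms" and hypothesizes that the app "will lead to improved HRV, pain, and mood symptoms compared with groups who do not use the app". The only pain instrument in the article is the Brief Pain Inventory (BPI). It appears under a section that opens "The following prescreening questionnaires will be administered to students to determine group classification", and again under Group Classification and Randomization, where it defines the CP group.

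**The concern.** A hypothesis about state mood over minutes needs a measure that refers to the present moment. A participant who follows a past-week instruction is asked at both time points about nearly the same seven days, so an honest answer has little reason to change whatever the app does. If scores do change, participants have departed from the stated window. The change could then be true state change or a response to expectation, and participants know whether they are holding a phone. A null result would say little about the app, and a positive one would be hard to interpret.

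On pain, a reader of the abstract would expect a between-arm pain result. With no named outcome or analysis behind that promise, any pain result reported later would be unplanned.

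**Working it through.** **The plan's own figure.** The article has one power calculation, N = 141 under Sample Size Estimation, and it concerns HRV. With f = 0.15, three phases, correlation 0.50 and alpha .05, the noncentrality is f² × N × m / (1 − ρ) = 0.0225 × 141 × 3 / 0.5 = 19.04. For a group-by-phase interaction with three groups this gives power 0.952. The smallest N is 140, which becomes 141 when rounded to a multiple of three. The figure therefore reproduces on that reading, but it has no bearing on mood or pain. The article gives no effect size, variance or power for Hypothesis 3.

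**Recall-window overlap.** Inputs: a single 12-minute exposure (abstract Methods; Limitations); rest and stress phases of 5 minutes each; inventories completed before and after the stressor and after the meditation (abstract Methods); a one-week recall window (POMS section).

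- One week = 7 × 24 × 60 = 10,080 minutes.
- The meditation as a share of the window: 12 / 10,080 = 0.12%.
- If the pre measure follows the stressor, the two windows are at least 12 minutes apart and share (10,080 − 12) / 10,080 = 99.88%.
- If the pre measure precedes the rest phase, the gap is at least 5 + 5 + 12 = 22 minutes and the overlap is 99.78%.
- Time spent on questionnaires and set-up is not stated. Assuming a gap as long as 60 minutes, the overlap is still (10,080 − 60) / 10,080 = 99.4%.

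The overlap describes the instruction, not the response. It shows that the two administrations ask almost the same question. It does not convert into a power figure, because nothing in the article says ratings behave as a time-weighted average of the window.

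**Fit of instrument to construct.** Other self-reports do match their purpose: the SUDS rates current distress, the Toronto Mindfulness Scale is described as a state measure, and the Mind-Wandering Inventory refers to the breathing task. Among the pre-post outcomes, the POMS is the one whose stated window conflicts with its hypothesis.

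**Tracing pain through the article.**

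| Place | Pain as an outcome? |
|---|---|
| Abstract, Objective | Yes: to be assessed, and hypothesized to improve |
| Introduction, aims paragraph | No: lists HRV, mind wandering, present moment awareness, mood, breath focus |
| Hypotheses 1a to 3 | No |
| Prescreening Questionnaires; Group Classification | BPI, for classification only |
| Secondary Outcomes list | No |
| Statistical Analyses of Outcomes | No |
| Exploratory Analyses | No |
| Limitations | Effects of repeated practice on pain left to future studies |

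**The case against.** The best defence on mood is that the POMS section describes the scale in general terms (items, subscales, reliability) and does not separately state the instruction used before and after the session. Hypothesis 3 itself says state. The Introduction also reports that, in the pilot, anxiety, anger and overall distress fell after the same 12-minute task, and those labels resemble POMS content. The recall sentence may therefore be a slip of description. This stands as a real possibility, but not as proof: the pilot's mood instrument is not named and no between-arm contrast is given. The two statements still conflict as written.

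A reader might infer that the mood question cannot be answered at all, or that Hypothesis 3 has power close to 5%. The documents support neither. The power statement would need participants to follow the instruction strictly and a model of how they answer, and the article gives no basis for computing it. The SUDS also gives a current distress/anxiety rating after meditation, so part of the question can be answered from data already planned.

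On pain, the defence is that this is an abstract out of step with a body that never lists pain as an outcome. That is fair, and it makes the repair simple. A reader might also infer that the BPI was certainly given only once. The text gives it only a prescreening role, but Figure 3, which shows questionnaire timing and names the BPI in its caption, is not available. A later administration cannot be ruled out, although it would still have no stated hypothesis or analysis.

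Finally, HRV is the primary outcome, and neither issue affects its analysis. That stands and limits the severity.

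**Conclusion.** The point holds in two separate parts.

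1. **Mood.** As written, Hypothesis 3 uses an outcome that does not measure its construct. The pre and post windows overlap by more than 99% for any gap up to an hour, so the measure is insensitive to the effect tested. Any movement would be hard to separate from expectation in an unblinded comparison. This rests on the POMS having been given with the instruction the article describes. If a right-now instruction was used, the fault is confined to one sentence. The loss of power cannot be quantified from the article.
2. **Pain.** The abstract states an objective and a hypothesis that no outcome, hypothesis or analysis in the body can test.

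This should be fixed but is not critical. It affects one secondary hypothesis and the stated objective, and leaves the primary HRV analysis intact.

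**What to change.** Document the following before outcomes by arm are examined. Data collection was already under way, with 189 participants recruited by July 2019, and a later change would look data-driven.

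1. **State the POMS instruction actually used.**
   - If participants were asked how they felt right now, correct the POMS section and keep Hypothesis 3 as it is.
   - If they were asked about the past week, test the state distress/anxiety part of Hypothesis 3 with the post-meditation SUDS, adjusted for baseline and post-stress SUDS, comparing the two conditions within CP and DA. Report the POMS descriptively, and state that state depression cannot be tested.
2. **Delete pain from the abstract's objective and hypothesis**, so that it matches the aims in the Introduction.

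Do not add a current-pain rating at this stage. With 41 CP participants recruited against a target of 60, about 60 − 41 = 19 remain, or 9 to 10 per arm, which would be nearly uninformative.

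**Cost.** The right-now branch and the pain deletion are wording changes. The past-week branch changes the outcome of a secondary hypothesis after most data are in, so it needs a dated amendment. It needs no new data, and its small downside is that the depression component is given up.
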